#### 2.2.2. Magnetic Resonance Imaging Set-Up

Magnetic resonance data will be acquired at a 1.5 T Siemens Magnetom Sempra Scanner (Siemens, Erlanger, Germany). A 12-channel transmit/receive knee coil is used to obtain images of the knee. The knee protocol includes six sequences: Proton density (PD)-weighted turbo spin echo (TSE) fat-suppressed (FS) in transversal (TRA), coronal (COR) and sagittal (SAG) plane, COR T1-weighted TSE, 3D Dual-echo Steady-State (DESS) water excitation (WE), SAG T2 mapping for knee cartilage, para-sagittal T2 mapping for ACL and 3D flow phase contrast (PC) for MR angiography (MRA) of the knee vessels. To obtain the highest quality images of the Achilles tendon (AT), a 16-channel transmit/receive head coil is used. The ankle protocol includes five sequences: SAG T1-weighted spin echo (SE), TRA T2-weighted TSE, COR T1-weighted TSE, SAG and TRA PD-weighted TSE FS, and SAG T2* mapping. The imaging parameters of the sequences are described in subsection Detailed magnetic resonance imaging protocol.

### 2.3. Protocol

#### 2.3.1. Global 4HAIE Protocol and Interactions

Prior to the laboratory visit, each participant will complete two sets of baseline socioeconomic and psychological questionnaires using the online Qualtrics platform (Qualtrics, Provo, UT, USA). The participants from South Bohemian control region will be transported 384 km to the Human Motion Diagnostic Center located in the experimental air-polluted (Moravian-Silesian) region by a laboratory car. Informed consent will be administered in person prior to the start of laboratory assessments.

On the first day of the laboratory visit, each participant is familiarized with the questionnaire smartphone application and the Fitbit device. Following this, participants complete a physical activity questionnaire, and a hair sample is collected. Blood pressure measurements, a graded exercise test, and respiratory capacity test are then performed. After dinner, each participant follows a standardized protocol for sleep assessment collected at the sleep laboratory.

The second day of laboratory visit starts with heart rate variability measurement, a questionnaire assessing the quality of sleep and an injury and pain survey. Prior to the physiological testing, each participant will complete fatigue questionnaires. During physiological testing, blood sample intake, bioimpedance measurements, and somatic measurements will be collected. After breakfast, cognitive function testing, DXA, and magnetic resonance imaging of the right ankle, right knee, and brain is performed. Finally, functional lower extremity tests and biomechanical testing are performed by each participant.

These baseline measurements are followed up for one-year using an online evaluation of physical activity through the Fitbit device, behavioral measures through a smartphone questionnaire app, as well as passively evaluated air pollution exposure. In addition, ecological momentary assessment is used and the pain and history of any running-related injury are evaluated through a brief survey administered on their smartphones.

#### 2.3.2. Biomechanical Protocol

Overground walking, running and treadmill running trials are completed in a counter-balanced order dependent on the number of participants during particular testing day. Subsequently, a cutting maneuver are performed. Reflective calibration and tracking markers are positioned on the pelvis bilaterally on the posterior superior iliac spines, and the anterior superior iliac spines. Markers are also positioned bilaterally on the lower limb on the medial and lateral malleoli, the medial and lateral femoral condyles, the greater trochanter of the femur and on four light-weight rigid plates with four markers per plate on the thigh and shank [35]. Markers are used to define the multi-segmental Rizzoli foot model on the right foot [36,37]. On the left foot rigid body model, a triad on the heel and markers on the first and fifth metatarsal heads are placed. Markers are attached on standard laboratory neutral running shoes (Brooks Launch 5, Brooks Sport Inc., Seattle, WA, USA). Delsys EMG sensors are placed over skin on the following muscles: rectus femoris, biceps femoris, gluteus medialis, and tibialis anterior (Figure 2). Prior to the biomechanics measurements, a standing calibration trial is recorded followed by a half-squat for EMG calibration.

Before measuring the biomechanics of running, the self-preferred speed is set. For runners, the question is: What is your usual speed when you go jogging for 45 min? Non-runners are asked to set the running speed at a pace that will allow them to run as far as possible (if they are unable to imagine the running pace for 45 min). Then, the participant runs at this pace for 2 min and in the last 30 s we measure the speed of 4 runs with photocells. The average of the four runs then indicates their self-preferred speed. Overground running consists of eight successful trials on a 17 m long runway at the participant’s self-preferred speed ±5%. Six successful trials at self-preferred speed will be collected for overground walking. The starting position for running trials is always set up at least (e.g., 7 m) from the force plate and for walking (e.g., 5 m). A successful walking/running trial consists of a participant landing on the force plate with the whole right foot. The subject’s starting position is fine-tuned so that they land in the middle of the pressure plate while walking normally at preferred velocity [38]. Additionally, subjects are instructed to focus on a distant point at eye level while walking, not on the pressure plate [39]. Participants run on the treadmill for 2 min at a fixed speed of 2.75 m/s. If the velocity corresponding to participant’s second ventilatory threshold (VT2) value from GXT is lower than 2.75 m/s, their speed is adjusted as follows: VT2 velocity is multiplied by 0.8. Subsequently, the speed of the belt is increased to 3.0 m/s or to the speed corresponding with the second ventilatory threshold from the VO_2_max test. The order of these two conditions is chosen depending on the speed (ascending). Both speed intervals are one-minute long with 30 s of recording.

Lastly, an unanticipated cutting maneuver is evaluated. For easy identification of the direction, a reflective tape is attached to the floor at an angle of 45° to the left side. A maximal approach speed is controlled using two photocells. For the unanticipated sidestepping task, photocell number 1 triggers a visual display to indicate if the participant will conduct a sidestep cut or proceed straight ahead. Photocell number 1 is placed at a calculated distance from the center of the force plate (90% of stride length plus an added distance for correction for the timekeeping signal delay based on the approach speed—0.2 s) (Figure 3). Participants are required to perform five successful running trials and five cutting unanticipated trials at the maximal self-preferred speed and then touch the mat at the end of the track as quickly as possible. Five successful cutting trials are collected after unanticipated trials presented in random order.

#### 2.3.3. Magnetic Resonance Imaging Protocol

In our protocol, each participant recruited for the study undergoes a right knee and right ankle scan. Firstly, the participant is asked to sign an informed consent form and is fully informed about the procedure of the examination. Subsequently, the participant is positioned feet first in supine position on the bed of the MRI scanner. The right knee joint is placed in the 12-channel knee coil and iso-centered in the scanner. The knee joint and ACL is evaluated qualitatively and quantitatively, and the total acquisition time (TA) is approximately 25 min.

In order to quantitatively analyze the knee cartilage and anterior cruciate ligament (ACL), the T_2_ mapping sequence in the SAG plane is used. The sequences for qualitative evaluation of the knee includes PD-weighted sequences in all three planes, T1-weighted in COR plane, 3D T2-weighted and 3D flow MRA. Imaging parameters for MRI sequences used for the knee are described in Table 1. The ankle joint scan with the main focus on the AT is performed in a 16-channel head coil with the designed device for fixing the leg at a 90-degree angle. Participants lie in a supine position with their ankle fixed and are asked to remain completely still during the scan. The acquisition time is approximately 20 min (Table 2).

#### 2.3.4. Functional Testing Protocol

Each participant will complete the following 5 physical examinations used in clinical practice: (i) Trendelenburg test for identification of hip abduction weakness during a single-leg stance position for 30 s. The pelvic-on-femoral position of the stance lower extremity is measured as the angle (°) between the anterior superior iliac spine and longitudinal axis of the femur for both side [40,41]. (ii) Knee anterior drawer test is used to test the laxity of the knee’s anterior cruciate ligament (ACL). The participant lie supine, hip flexed to 45°, knee flexed to 90°. Anterior—posterior displacement of the tibia relative to the thigh will be measured [42]. The displacement is graded relative to the contralateral side. The displacement is evaluated based on International Knee Documentation Committee (IKDC) categories as normal (-), nearly normal (+), abnormal (++), and severely abnormal (+++) [43]. (iii) Ankle anterior drawer test is used to test the ligament of the anterior talofibular. The participant lies supine, ankle in 10–15° plantar flexion. The posterior displacement of the heel relative to the distal tibia is measured [44]. The displacement is graded relative to the contralateral side. The participants are classified into three grades. Grade I (-) is defined as a stable joint, grade II is a partially unstable joint with two different displacements of the heel relative to the distal tibia (+); (++) and grade III is a completely unstable joint (+++). (iv) The lunge test is used to assess the dorsiflexion range of the movement. The participant is in a standing position facing a wall. Tested foot and knee are perpendicular to a wall, the opposite limb is in tandem position. Participants are instructed to perform a lunge when the knee is in contact with the wall while the heel is still in contact with the ground. The distance between the great toe and the wall is measured (cm) [45]. (v) The kick a ball test determines functional dominance. The participant kicks a ball 3 times into the marked goal area. The lower extremity that is used for most trials is identified as the dominant limb [46].

### 2.4. Data Analysis

#### 2.4.1. Biomechanics Data Analysis

The kinematic and kinetic data is processed using QTM (Track Manager; Qualisys, Sweden, Göteborg) and Visual3D software (C-Motion, Germantown, Kentucky, KY, USA,). Walking, running and cutting main gait events are based on the automatic gait event identification [47]. Ground-reaction force and marker kinematic data is filtered using a fourth-order Butterworth low-pass filter with a cut-off frequency of 50 Hz (analog ground reaction force data) and 12 Hz (kinematics) for overground running trials, 40 Hz and 8 Hz for treadmill running and overground walking trials, and 50 Hz and 15 Hz for cutting trials [48]. This cut-off frequency was selected based on previous literature, residual analysis and visual inspection of pilot data [48,49,50,51]. The proximal and distal ends and the coordinate systems of the lower extremity segments and pelvis are determined from the calibration trial [52]. Hip, knee, and ankle three-dimensional joint angles are calculated using an x-y-z Cardan rotation sequence. Angles in the lower extremity joints are determined throughout the entire stance phase and whole gait cycle. The three-dimensional net internal ankle, knee, and hip joint moments are calculated using a Newton–Euler inverse dynamics technique [53].

Electromyography (EMG) patterns are recorded during the overground walking and running and cutting trials using surface electrodes (Delsys Inc., Boston, MA, USA). Data from major surface muscles of the lower extremities, rectus femoris, biceps femoris, gluteus medialis, and tibialis anterior are collected. The raw EMG signals from all type of movement are processed using a band-pass filter (50–450 Hz), rectified, and consequently passed through a critically damped low-pass filter with a 20 Hz cut-off [54]. The signal is then normalized to the peak processed signal found during standardized squat.

#### 2.4.2. Magnetic Resonance Imaging Data Analysis

Semi-quantitative assessment of cartilage on MRI images is performed by an expert musculoskeletal radiologist ([name], 10 years of experience) using the modified Outerbridge grading of chondromalacia [55]. This grading system is divided into five grades by MRI (0—physiological state, 1—focal areas with hyperintensity, 2—swelling of articular cartilage extending to surface, 3—partial-thickness cartilage loss, and 4—full-thickness cartilage loss). The modified Outerbridge grading of chondromalacia is widely used for morphological analysis of cartilage in clinical trials as well as in epidemiological studies [56,57,58]. The cartilage assessment is conducted in 14 anatomical regions (two patellar, six femoral, and six tibial): lateral/medial patella, lateral/medial anterior femur (AF), lateral/medial central femur (CF), lateral/medial posterior femur (PF), lateral/medial anterior tibia (AT), lateral/medial central tibia (CT), lateral/medial posterior tibia (PT). The ACL is assessed semi-quantitatively as follows: 0—physiological state, 1—primary signs of ACL contusion (swelling, fiber discontinuity), 2—partial ACL tear, and 3—total ACL tear [59,60]. To evaluate the AT, all subjects are rated using Vienna morphological achilles tendon score (VIMATS; 0–100, worst to best) [61]. As reported by Apprich et al. [61], thickness, continuity, signal intensity, and associated pathologies is evaluated.

For the quantitative analysis, T2 maps of knee cartilage and ACL are calculated by mono-exponential fitting of the signal intensity decays on a pixel-by-pixel basis. Knee cartilage and ACL is manually segmented from T2-weighed images by two readers blinded to morphological findings ([name], [name] supervised by [name]) using a segmentation and analysis tool built using MATLAB software (Mathworks Inc., Natick, MA, USA). Knee cartilage is divided into regions-of-interest (ROIs) similar to the regions used in the modified Outerbridge grading of chondromalacia. A similar set up of quantitative analysis as reported in [62,63] is used. ACL is divided into four regions-of-interest (ROIs): insertion, middle, upper, and whole ACL. Average T2 relaxation times of cartilage and ACL are calculated for each ROI.

In order to quantitatively assess the AT, ROIs are manually drawn from sagittal images by two readers ([name] and [name], supervised by [name]) in three regions: insertion part (INS), middle part (MID), and muscle-tendon junction (MTJ). The ROIs are drawn in MatLab (MathWorks, Natick, MA, USA). Total length of each part is selected as one-third of the total length of AT. Values from ROIs are analyzed by mono- and bi-exponential fitting procedure in Interactive Data Language (IDL 6.3, Boulder, CO, USA). Set-up of these analyses is described in more detail in [64].

## 4. Discussion

We introduced the biomechanical and musculoskeletal imaging protocol designed to investigate the musculoskeletal and neuro-mechanical health in the 4HAIE human cohort. It has been suggested [65] that the last 45 years of research on running musculoskeletal injuries tended to focus only on mechanical loading while the musculoskeletal tissues properties and the specific social and environmental factors have been neglected [65]. The protocol for this study might reveal new knowledge, especially in the following globally investigated issues related to the health and quality of life of the population.

Ecological momentary assessment and one-year online monitoring using IT technologies will allow us to uniquely examine the interplay of biomechanical, physiological, anatomical, psychosocial, and environmental factors affecting running injuries. Although research on running injuries may seem like a negligible reason for such an extensive study, it is muscle skeletal injuries that can be the cause of a significant decline in physical activity during older adulthood [12]. Secondly, we would like to investigate the possible associations between physical activity, air pollution and musculoskeletal tissues degeneration (knee cartilage, ACL, and AT). Only such an extensive study, which also examines psychosocial and physiological covariates, can indicate whether the conclusions about the impact of air pollution on musculoskeletal health in previous animal studies and uncontrolled human studies are robust [3,6].

One of the possible examples of hypotheses which could be evaluated based on this one-year prospective study is that the external environment (air pollution) will influence the incidence of running related injuries. Interactions between psychosocial and physiological variables may exist, and these interactions may result in a higher incidence of running injuries especially in the air polluted region compared with the control region. Another possible hypothesis which could be addressed based on baseline cross sectional study is that the decrease in physical activity in older age may be related to gait biomechanics and the degeneration of dominant musculoskeletal structures such as knee cartilage and Achilles tendon. Moreover, we hypothesize that knee cartilage and Achilles tendon degeneration related to aging may be associated with a healthy lifestyle and environment. Specifically, we hypothesize that runners in the air polluted region will have different properties of knee cartilage and Achilles tendon compared with inactive controls and this difference between runners and inactive individuals will not be equally large in the control unaffected region. It can also be determined whether AT and knee cartilage degeneration is associated with running/in-activity status and whether air pollution status affects this association. We can adjust for potential confounders in statistical analyses: biomechanical load, physical activity, aerobic fitness, history of running related injury, etc.

The patterns of kinematics, kinetics and electromyographic activity during walking, running and cutting maneuvers allow a comprehensive description of possible biomechanical loads during locomotion and change of direction. The measured curves are in accordance with the results presented in previous studies [54,66,67,68,69]. In addition, the ranges and maxima of angles, moments, and EMG are in accordance with the intensity of individual movement tasks (walking lowest intensity, running medium intensity, and cutting maximum intensity). Discrete biomechanical variables derived from the presented curves (e.g., initial contact angles, maximum moment values, net joint powers, coordination variability, etc.) can be used in multidimensional statistical models to identify factors affecting musculoskeletal injuries.

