Air pollution and health: Active transportation provides a substantial health benefit because of increased physical activity (PA) [4]. However, active travel may increase the intake of air pollution leading to negative health consequences [5]. A recent study found that the severity of osteoarthritis could be promoted by air pollution via systemic inflammatory mechanisms [6]. In addition, pollution from traffic may be an environmental risk factor for rheumatoid arthritis [7]. An increased risk of rheumatoid arthritis in participants exposed to PM2.5 and NO_2_ was detected in a retrospective study in Taiwan [8]. Air pollution has been associated with the incidence of arthritis. However, whether this environmental factor is causally linked with osteoarthritis in humans, still remains a matter of debate. Muscular skeletal diseases such as knee osteoarthritis may develop over several decades and have been shown to be associated with biomechanical load during gait [9]. It has been shown that the knee adduction moment during gait leads to higher knee cartilage degeneration [10]. In addition, it has been shown that higher walking cadence is associated with less cartilage osteoarthritis progression [11]. Especially given that biomechanical data processing is challenging, the biomechanical research to date has tended to focus on small samples rather than multidisciplinary epidemiological research. Multidisciplinary epidemiological research can help control for psychosocial, physiological, or behavioral potentially biasing variables.

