In addition, prospective cohort studies show that a minimum of 18% and a maximum of 92% of runners incur injuries during this activity [15]. The risk of injury and illness associated with running limits the use of the potential offered by this activity in health management for the current population. There are only a few prospective biomechanical studies focusing on running [15,16,17,18,19,20]. None of these studies apply control group, multidisciplinary approaches and the number of test subjects investigated is lower than 500. A prospective cohort study of a large number of runners, combined with a multidisciplinary approach (epidemiology, biomechanics, physiology, psychosociology), has the potential to reveal the causes of the most common chronic injuries in relation to air pollution. Among the most common injuries associated with running are Medial tibial stress syndrome, Achilles tendinopathy, Plantar fasciitis, Patellar tendinopathy, ankle sprains, and Iliotibial band syndrome [15]. All these injuries lead to a cessation of regular motion activity, and they may negatively influence adherence to physical activity.

During locomotion, it is often necessary to change direction or alter the direction of motion resulting from some external stimulus. However, such movements, often referred to as ‘cutting’, result in injuries particularly to the knee. A prominent knee injury, anterior cruciate ligament (ACL) rupture frequently occurs in non-contact, rapid movement situations such as cutting maneuvers in sport [21]. Females show greater ACL injury rates than males [22,23,24] and the prevalence of ACL injury increases over time in the female population [25]. Previous investigations [26,27] have shown that air pollution is associated with a decrease in neuro-behavioral functions and the level of gross and fine motor skills in children. Changes in neuro-behavioral function and the level of motor skills could influence associative risk factors of the ACL injury as well as movement coordination and its variability. Successfully negotiating a high ACL injury risk requires complex neuromuscular control strategies for dynamic joint stabilization [28]. Moreover, situational awareness, arousal, and attentional resources of the individual may influence areas of neurocognitive function, affecting the complex integration of vestibular, visual, and somatosensory information needed for neuromuscular control [28].

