#### 2.1.1. Inclusion Criteria for Active Runners

Active runners must spend at least 150 min a week in moderate-intensity physical activity or 75 min in high-intensity physical activity (or an equivalent combination of moderate- and vigorous-intensity activity), including running [34]. They must run regularly for 6 weeks or longer, at least 10 km per week, and plan to continue running for another 12 months. Participants must also be between 18–65 years of age upon enrollment, reside in the given localities year-round for at least 5 years, and have no plan to move from the given locations in the next 12 months. Participants must have internet access and own a smartphone (with Android 5.0 or higher, or iOS operating systems) with a data connection (Wi-Fi or mobile data).

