#### 2.1.2. Inclusion Criteria for Inactive Controls

Inactive controls fulfill the same criteria as active runners, but, in spite of being otherwise capable of physical activity including running (i.e., having no limitations to physical activity diagnosed by their physician), they do not meet public health recommendations for physical activity (i.e., engage in physical activity for less than 150 min a week).

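### Physical activity, aerobic fitness and biomechanical load are labelled confounders of running status, but the first defines the groups and the others probably follow from running

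*Protocol article*

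**What the plan says.** Section 4 (Discussion) of the protocol article sets out candidate hypotheses. One is "whether AT and knee cartilage degeneration is associated with running/in-activity status and whether air pollution status affects this association". Its specific form is a runner-by-region interaction: runners in the polluted region differ from inactive controls, and "this difference between runners and inactive individuals will not be equally large in the control unaffected region". The last sentence of that paragraph names the adjustment variables: "We can adjust for potential confounders in statistical analyses: biomechanical load, physical activity, aerobic fitness, history of running related injury, etc". No other sentence in the article lists a set of covariates.

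The groups are defined in sections 2.1.1 and 2.1.2. "Active runners must spend at least 150 min a week in moderate-intensity physical activity", or 75 minutes at high intensity, or an equivalent mix, besides a minimum running distance. Inactive controls fall short of the recommendation; that is, they "engage in physical activity for less than 150 min a week".

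The Introduction adds two relevant statements. On load, it says that the "knee adduction moment during gait leads to higher knee cartilage degeneration". Its paragraph on aims makes the effect of pollution on the biomechanics of movement a specific purpose of this protocol.

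**The concern.** A confounder precedes the exposure, or at least is not caused by it, and it affects the outcome. Physical activity fails this test for the runner/inactive contrast because it is the variable on which the contrast is cut. Aerobic fitness and biomechanical load are doubtful for a different reason: both plausibly change when a person runs regularly, and the article itself places gait load on the path to cartilage degeneration. Load is also a stated target of the pollution effect, so the same doubt arises when region is the exposure.

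A model that includes these variables answers a narrower question: what difference remains between runners and inactive people at the same activity, fitness and load. That can be a legitimate question, but it is not the one posed. A reader of the resulting paper could take a small or reversed coefficient as evidence that running has little to do with tissue quality, when the model had held constant the routes by which running acts.

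**Working it through.** The article gives no effect size, SD or power for this analysis, so there is no figure of its own to reproduce. The check has two parts.

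**Role of each variable, from the article's own text**

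| Variable | What the article says | Role for running status → tissue |
|---|---|---|
| Physical activity | Defines both groups (2.1.1, 2.1.2) | Part of the exposure |
| Aerobic fitness | Measured at baseline, no causal statement | Likely mediator |
| Biomechanical load | Leads to cartilage degeneration; an outcome of pollution (Introduction) | Likely mediator |
| Running-injury history | "All these injuries lead to a cessation of regular motion activity" (Introduction) | Possibly both confounder and mediator |

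**Illustrative size**

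From the article (2.1): 900 runners and 600 inactive controls, 750 per region. If both groups split equally by region, each region has 450 runners and 300 controls.

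Assumed, not from the article: runner effect 0.40 SD in the control region; runner-by-region interaction 0.30 SD, so 0.70 SD in the polluted region; residual SD 1; a gap *d* in physical activity between groups of 1.5 or 2.5 within-group SDs, the same in both regions; and a share *s* of both effects carried by activity.

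1. *Activity as a main effect.* The slope of outcome on activity is 0.40*s*/*d* in the control region and 0.70*s*/*d* in the polluted region. A single slope averages them: 0.55*s*/*d*. Multiplying by the gap *d* and subtracting gives the adjusted runner coefficient in the control region, 0.40 − 0.55*s*.
2. *Interaction under the same model.* The same amount is subtracted in both regions, so (0.70 − 0.55*s*) − (0.40 − 0.55*s*) = 0.30 for every *s*.
3. *Activity and activity-by-region both entered.* Each region has its own slope. The interaction becomes 0.30(1 − *s*), and the runner coefficient in the control region becomes 0.40(1 − *s*).

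| Share *s* | Runner, activity as main effect | Interaction, activity as main effect | Runner, with activity-by-region | Interaction, with activity-by-region |
|---|---|---|---|---|
| 0% | 0.40 | 0.30 | 0.40 | 0.30 |
| 25% | 0.26 | 0.30 | 0.30 | 0.23 |
| 50% | 0.13 | 0.30 | 0.20 | 0.15 |
| 75% | −0.01 | 0.30 | 0.10 | 0.08 |
| 100% | −0.15 | 0.30 | 0 | 0 |

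A simulation with 200 replicates per setting agrees. Under main-effect adjustment the runner coefficient was 0.39 to 0.42, 0.26 to 0.27, 0.13, −0.01 to −0.03 and −0.14 to −0.15, with the interaction at 0.28 to 0.30 throughout. With activity-by-region entered, the interaction was 0.28 to 0.29, 0.23 to 0.24, 0.14 to 0.16, 0.08 to 0.09 and about 0.

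The sign change needs *s* above 0.40/0.55 = 73%. It arises because one pooled slope over-corrects in the control region; with region-specific slopes the coefficient shrinks towards zero without crossing it.

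*Precision.* The unadjusted SE of the runner coefficient is √(1/450 + 1/300) = 0.075. With activity in the model it is √(1/450 + 1/300 + *d*²/1500), which is 0.084 for *d* = 1.5 and 0.099 for *d* = 2.5. For the interaction, the SE is √[2(1/450 + 1/300)] = 0.105 without the activity-by-region term. With it, the SE is √[2(1/450 + 1/300 + *d*²/750)], or 0.131 and 0.167.

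**The case against.** The strongest reply is that no model has been fixed. The sentence stands in the Discussion, says only that adjustment is possible, calls the variables potential confounders and leaves the list open. A journal article may leave the covariate set to a fuller plan. This stands, and it limits the severity. It does not make the label right: the article does say something about these variables, and for physical activity what it says is wrong for this contrast.

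Second, the study has other exposures. One hypothesis is that "the external environment (air pollution) will influence the incidence of running related injuries". There, baseline activity, fitness and injury history are at least arguable adjustment variables. This also stands. The point is confined to running status and its interaction with region, with the added caution that biomechanics is a declared outcome of pollution.

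Four stronger readings are tempting, and the article does not support them:

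- *Adjustment removes the effect under study.* How much is lost depends on a mediated share that nobody knows, and the interaction, which is the specific hypothesis, need not move at all.
- *All four listed variables are mediators.* The article says injury stops people from being active, so injury history can precede and determine inactive status. The tissue data are cross-sectional, so the order is not observed.
- *Runners and controls never share an activity value.* A runner may qualify on 75 minutes at high intensity while a control may report anything below 150 minutes, so raw minutes can overlap between 75 and 150. Later Fitbit data need not respect the entry cut either.
- *Age, sex and social position will be left out.* The list is open, age and sex are quota variables (2.1), and socioeconomic questionnaires are collected (2.3.1).

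**Conclusion.** The point holds, at moderate severity. For the association of running status with cartilage and tendon properties, the article labels as confounders one variable that defines the exposure and two that probably follow from it. Adjusting for them would change the estimand from the total to a direct association.

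In the illustration the runner-inactive difference in the control region falls from 0.40 SD to 0.13 SD when half of it runs through activity, and reverses in sign above a share of about 73% if a single activity slope is fitted. These sizes rest on the assumed effects, on an equal split of runners and controls by region, and on an activity gap that is the same in both regions. If the gap differed by region, main-effect adjustment would also shift the interaction, by the pooled slope times the difference in gaps. The classification of physical activity rests on no assumption beyond the inclusion criteria. That of fitness and load is a plausible causal reading which the cross-sectional data cannot confirm.

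**What to change.** Replace the sentence in section 4, and carry the same rule into the analysis plan, along these lines:

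> For the association of running status with cartilage and Achilles tendon properties, and for its interaction with region, the main models estimate the total association and adjust for age, sex and socioeconomic status. Physical activity, aerobic fitness and biomechanical load are not included in these models. They enter only a separate analysis, labelled as mediation or direct effect, which states whether covariate-by-region terms are fitted. Running-injury history may be both confounder and mediator; results are reported with and without it, and injury before taking up running is separated from injury after it where the data allow.

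For the pollution hypotheses, state the exposure of each and say which of the listed variables are treated as confounders and which as mediators.

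The cost is a change of wording and one extra secondary model. The adjustment variables for the main models are already collected. Dating injury relative to the start of running depends on what the injury survey records, which the article does not say.
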